### 7.4.1.3 UV-dose measurements

Because the major determinant of artificial UV exposure will be time spent at desk each week and body surface exposed area, this will be recorded daily using a daily diary (see Figure 7), in which all subjects (also those in the control group) will self-report desk presence time and time spent outside in the morning and afternoon of their working day, and give an indication how much body surface areas was exposed during that day. Time spent outside during daylight in the weekend will also be reported on Monday.

Together with KNMI data we will be able to estimate the natural UVB exposure of the participant and provide for an analysis whether both groups behave similarly in their natural UVB dose. However, natural UVB exposure is expected to be minimal during the study months in autumn and winter (see [39])

Participants will gently be reminded to fill in the daily diary every day towards the end of the day. At the end of the week, they will receive a link to upload a scan or photo of the completed daily diaries or they can do this daily via a link provided at the start of the study.

|                                                  |               |              |               |              |               |              |               |              |               |              |
|--------------------------------------------------|---------------|--------------|---------------|--------------|---------------|--------------|---------------|--------------|---------------|--------------|
| Daily diary    week 1                            |               |              |               |              |               |              |               |              |               |              |
|                                                  |               |              |               |              |               |              |               |              |               |              |
| Estimated Desk Presence & Estimated Time Outside |               |              |               |              |               |              |               |              |               |              |
| Time/Day                                         | Monday        |              | Tuesday       |              | Wednesday     |              | Thursday      |              | Friday        |              |
|                                                  | Desk presence | Time outside | Desk presence | Time outside | Desk presence | Time outside | Desk presence | Time outside | Desk presence | Time outside |

|                                                                                  |                       |                       |                       |                       |                       |                       |                       |                       |                       |                       |
|----------------------------------------------------------------------------------|-----------------------|-----------------------|-----------------------|-----------------------|-----------------------|-----------------------|-----------------------|-----------------------|-----------------------|-----------------------|
| 08:50-13:00                                                                      | __ hour(s)
__ min. | __ hour(s)
__ min. | __ hour(s)
__ min. | __ hour(s)
__ min. | __ hour(s)
__ min. | __ hour(s)
__ min. | __ hour(s)
__ min. | __ hour(s)
__ min. | __ hour(s)
__ min. | __ hour(s)
__ min. |
| 13:00-17:10                                                                      | __ hour(s)
__ min. | __ hour(s)
__ min. | __ hour(s)
__ min. | __ hour(s)
__ min. | __ hour(s)
__ min. | __ hour(s)
__ min. | __ hour(s)
__ min. | __ hour(s)
__ min. | __ hour(s)
__ min. | __ hour(s)
__ min. |
| Weekend exposure                                                          |                       |                       |                       |                       |                       |                       |                       |                       |                       |                       |
| Total time outside between 8:50 and 17:10
Saturday                     | __ hour(s)
__ min. |                       |                       |                       |                       |                       |                       |                       |                       |                       |
| Total time outside between 8:50 and 17:10
Sunday                       | __ hour(s)
__ min. |                       |                       |                       |                       |                       |                       |                       |                       |                       |
| Body Surface Area (BSA) exposure (Mark with X which body area is exposed) |                       |                       |                       |                       |                       |                       |                       |                       |                       |                       |
|                                                                                  | Monday         | Tuesday        | Wednesday      | Thursday       | Friday         |                       |                       |                       |                       |                       |
| Front Face                                                                       |                       |                       |                       |                       |                       |                       |                       |                       |                       |                       |
| Neck                                                                             |                       |                       |                       |                       |                       |                       |                       |                       |                       |                       |
| Hands                                                                            |                       |                       |                       |                       |                       |                       |                       |                       |                       |                       |
| Lower arms                                                                       |                       |                       |                       |                       |                       |                       |                       |                       |                       |                       |
| Upper arms                                                                       |                       |                       |                       |                       |                       |                       |                       |                       |                       |                       |
| Other, namely                                                                    |                       |                       |                       |                       |                       |                       |                       |                       |                       |                       |
| To be filled in by study manager                                          |                       |                       |                       |                       |                       |                       |                       |                       |                       |                       |
| % occupation                                                                     |                       |                       |                       |                       |                       |                       |                       |                       |                       |                       |
| %BSA                                                                             |                       |                       |                       |                       |                       |                       |                       |                       |                       |                       |
| % time natural UV-B                                                              |                       |                       |                       |                       |                       |                       |                       |                       |                       |                       |

**Figure 7:** Example of the diary to be filled in daily

### **7.5 Withdrawal of individual subjects**

Subjects can leave the study at any time without giving a reason if they wish to do so without any negative consequences. In the event that a subject stops before data assessment week 4, an attempt will be made to recruit a new volunteer (if available) who can start his/her first measurements in week 4.

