### 3.1 Duration of the study

The study protocol consists of a baseline measurement (Day 0 ) and an 8-week intervention period. Three data assessments will be conducted in day 1 of week 0, day 29-31 of week 4 and day 58-60 of week 8. Each data assessment is expected to take about 20-30 minutes. In addition to these three measurement points, participants are asked to complete a short (<1 minute) diary each day about desk presence, time spent outside, and clothing. The study is scheduled for autumn or winter 2020. This season has been chosen as both serum 25(OH)D and outdoor UV intensity start to decline rapidly to negligible values in this period [39,40].

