Before the start of the execution of the study protocol, participants who adhere to the inclusion criteria will be contacted and informed about the study by the research team and provided the opportunity to ask questions. At the end of this meeting, participants are asked to read the participant information again in their own time and send back the signed informed consent form if they decide to participate. In this consent form, participants also sign for transfer of their home address (contact details) to Signify, only with the goal to make an appointment to install the luminaire at their home office. Participants can ask any questions regarding the study via e-mail or phone before deciding to participate. Furthermore, the researcher will emphasize that it is always possible to stop at any time during the study without the necessity to explain choices, without any further consequences. After deciding (within 3-5 days after being informed by the researcher) to participate and signing the consent form, the researcher will inform the participants on which three days the data collection will occur (blood sampling and main questionnaire). Ideally, the blood sampling occurs on the same day of the week, at approximately the same time. Participants will inform the researcher at which timeslot they are available for the blood sampling, and if desired, the researcher can plan an appointment at DVU for the participant. Alternatively, participants can also make an appointment at DVU themselves (online) where they choose a time that fits in their schedule. In case enough participants meet the in- and exclusion criteria (at least 28), block randomization will be used by the responsible researcher to assign participants to the two conditions. In case there are insufficient participants who can guarantee at least 2.5 days of desk presence in the home office, participants with at least 2.5 days of desk presence will first be assigned to the intervention condition (based on timing of sending back the informed consent form) and remaining participants will be assigned to the control condition.

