## 9. STATISTICAL ANALYSIS

The data analyses consist of multiple steps. All data will be presented quantitatively.

As a first step, we will inspect the distribution of the variables of interest. A Shapiro-Wilk test will be conducted to inspect normality of the variables. If needed and possible, a transformation of the scores will be performed to adhere to the assumption related to normality for the statistical analyses. Subsequently, an outlier detection will be performed with outliers determined as values more than 3 SD's from the mean.

Next, we will provide the descriptive statistics for the experimental and control condition for the variables measured only at baseline (see Table 1), as well as for the dependent variables (i.e., the variables for the primary (serum 25(OH)D) and exploratory research objectives (fatigue and sleep), see Section 2.) for each of the measurement points. Comparisons of the variables at baseline will be investigated via independent samples T-test to examine whether there were significant differences between the two groups for any of the variables at measured baseline. If the data appears to be not normally distributed and no transformation is applicable, we will employ a non-parametric test (Mann-Whitney test).

Subsequently, the main research objective (i.e., effects of the light intervention on serum 25(OH)D at week 8) will be investigated using an ANCOVA analyses with the intervention (yes/no) as predictor and change scores in serum 25(OH)D as outcome variable. This analysis will further be controlled for average desk presence and time spent outside. In case data is non-normally distributed a non-parametric test (Mann-Whitney test) will be conducted taking into account the limitation that this analysis cannot control for the mentioned confounders. Analyses will only be conducted with data from participants with both the baseline measurement and the final measurement point available. An alpha level of 0.05 will be used as criterion.

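### Replacements who enter in week 4 can join the primary analysis with a change score that is not the planned day 0 to week 8 change

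*Protocol*

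**What the plan says.** Section 3.1 fixes the schedule: "The study protocol consists of a baseline measurement (Day 0 ) and an 8-week intervention period", and "Three data assessments will be conducted in day 1 of week 0, day 29-31 of week 4 and day 58-60 of week 8". The same section explains the season was chosen because serum 25(OH)D is then falling fast.

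Section 7.5 adds a contingency for anyone who stops before the week 4 assessment: "an attempt will be made to recruit a new volunteer (if available) who can start his/her first measurements in week 4". It is silent on the new volunteer's arm, the method of allocation and the date of the last sample.

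Section 7.4 describes allocation for the starting pool: if at least 28 people are eligible, "block randomization will be used by the responsible researcher to assign participants to the two conditions". Section 4.4 limits the trial to 14 lamps and hence 14 people per group.

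Section 9 states the main objective as "effects of the light intervention on serum 25(OH)D at week 8", tested by "ANCOVA analyses with the intervention (yes/no) as predictor and change scores in serum 25(OH)D as outcome variable". On covariates: "This analysis will further be controlled for average desk presence and time spent outside". On the analysis set: "Analyses will only be conducted with data from participants with both the baseline measurement and the final measurement point available". Replacements are not mentioned.

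**The concern.** The primary outcome is a change score in a series that falls steeply with the season, so a score means the same thing in two people only if it spans the same dates. A volunteer first sampled in week 4 cannot supply the planned change. Ending in study week 8 gives a 4-week change from an already lower level. Ending in week 12 gives 8 weeks, but over a later stretch of the decline.

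Section 9 asks only for a baseline and a final measurement, and a week-4 entrant can be read as having both. Neither covariate describes when the person started or for how long they were followed, so the model cannot correct the mismatch. If replacements are uneven between arms, the treatment contrast shifts for reasons unrelated to the lamp. If they are even, the spread within each arm still grows, in a trial already run with 14 per group where section 4.4 calculated 17.

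**Working it through.** **The plan's own figure.** Section 4.4 gives a difference of 8.8, SD 8.4, alpha 0.05, power 0.90 and 17 per group. The standardised difference is 8.8/8.4 = 1.048. A t-test calculation gives n = 16.3, so 17, with a one-sided alpha of 0.05, and n = 20.2, so 21, with a two-sided alpha. The 17 is therefore reproduced one-sided. The text does not state sidedness and Figure 3 is not shown, so both are given below. With 14 per group, power is 85% one-sided and 76% two-sided.

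**Control level at week 4.** Table 2 gives each effect in nmol/L and as a percentage. At week 8 the percentages are relative to the control level of 44.1: 17.6/44.1 = 40%, 13.6/44.1 = 31%, 8.8/44.1 = 20%, 5.5/44.1 = 12%. On the same basis, and allowing half a point of rounding in the percentages, the week-4 rows imply:

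| Effect at week 4 | Printed % | Implied control level |
|---|---|---|
| 12.4 | 23 | 12.4/0.235 to 12.4/0.225 = 52.8 to 55.1 |
| 8.8 | 17 | 8.8/0.175 to 8.8/0.165 = 50.3 to 53.3 |
| 6.2 | 12 | 6.2/0.125 to 6.2/0.115 = 49.6 to 53.9 |
| 3.8 | 7 | 3.8/0.075 to 3.8/0.065 = 50.7 to 58.5 |

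All four hold only for 52.8 to 53.3; the midpoint is 53.05.

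**Change scores if follow-up ends in study week 8.** Start 66.4 and control end 44.1 come from Figure 2.
- Control, weeks 0 to 4: 53.05 − 66.4 = −13.35.
- Control, weeks 4 to 8: 44.1 − 53.05 = −8.95 (range −8.7 to −9.2), against −22.3 over 8 weeks. The gap is 22.3 − 8.95 = 13.35, or about 13.4.
- Intervention replacement: −8.95 + 6.2 = −2.75, against −13.5. The gap is 10.75. This assumes the 4-week effect of 6.2 in the planning scenario also applies when exposure starts in week 4.

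**Effect on an arm of 14.** The protocol gives no drop-out rate, so one or two replacements per arm are assumed.
- Each control replacement moves the arm mean by 13.35/14 = 0.95, which is 11% of 8.8. Each intervention replacement moves it by 10.75/14 = 0.77 under the planned effect, or by 0.95 if the lamp does nothing.
- Control-arm SD with two replacements: √(8.4² + 13.35² × (2/14)(12/14)) = 9.6.

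Power below comes from 200,000 simulated trials per row, using an unadjusted t-test and SD 8.4:

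| Replacements (intervention, control) | Expected contrast | Power one-sided / two-sided |
|---|---|---|
| 0, 0 | 8.8 | 85% / 76% |
| 0, 1 | 7.8 | 75% / 63% |
| 0, 2 | 6.9 | 63% / 49% |
| 1, 0 | 9.6 | 89% / 81% |
| 2, 0 | 10.3 | 92% / 86% |
| 1, 1 | 8.6 | 81% / 70% |
| 2, 2 | 8.4 | 77% / 63% |

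The higher power for intervention-arm replacements is bias, not information. With no true effect, two such replacements create a spurious difference of 2 × 0.95 = 1.9 nmol/L, and the test rejects in about 12% of trials one-sided (7% two-sided) instead of 5%.

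**Without replacement.** The contrast stays at 8.8 if those lost resemble those who stay. Power one-sided / two-sided is 84% / 74% for 13 against 14, 83% / 72% for 12 against 14, and 80% / 69% for 12 against 12.

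**If follow-up runs to study week 12.** The interval is 8 weeks, shifted by four. The protocol gives no control level for week 12, so the mismatch cannot be sized.

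**The case against.** The strongest reply is that section 7.5 can be read as starting the full three-sample series in week 4. Section 7.1.1 defines the later samples as taken after 4 and 8 weeks of the intervention, and the September-to-January window in section 11.4 may leave room for a later finish. The figures above would then not apply. This stands as a limit on the numbers. It does not rescue comparability, because the change would still cover different dates and the model has no term for them.

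It can also be said that a week-4 entrant has no day 0 sample and so fails section 9's requirement. That reading is possible, but section 9 does not say so.

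Replacement is attempted only if a volunteer is available, and balanced replacement leaves little bias. Both points stand and lower the severity.

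Three stronger readings are tempting but not supported:
- *Replacements are unrandomised.* Section 7.5 does not say how they are allocated, and section 7.4 says generally that eligible participants are randomised. With 14 lamps and 14 places per arm, a late entrant would probably take the arm of the person who left, but that is an inference.
- *The replacement rule removes drop-outs from the analysis.* The requirement for baseline and final data in section 9 does that, with or without section 7.5.
- *The bias in the arm mean is as large as the treatment effect.* The 13.4 gap applies to one person's change score; the arm mean moves by about a fourteenth of it.

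**Conclusion.** The point holds in a limited form. Section 7.5 permits entrants whose change score, on either reading of their follow-up, is not the planned day 0 to week 8 change, and section 9 neither excludes them nor adjusts for the difference.

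Under the week-8 reading, one or two replacements confined to the control arm reduce the expected contrast by 11% or 22%. Confined to the intervention arm, they raise it by 9% or 17%. For two vacated control places, replacing them leaves 49% two-sided power, while leaving them empty keeps 72%, so on this reading the rule works against its apparent purpose.

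These figures rest on the simulated levels in Figure 2 and Table 2, an assumed one or two replacements per arm, and an unadjusted comparison. Under the week-12 reading the direction of concern is the same but the size is unknown. Because this is a contingency of unknown frequency, it should be fixed but is not critical.

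**What to change.** 1. In section 7.5, delete the week-4 replacement sentence. If it is kept, state the replacement's arm, how it is assigned and the sampling dates, and say that week-4 entrants are left out of the primary analysis and used only in a sensitivity analysis.
2. In section 9, restrict the primary analysis to participants with a day 0 sample and a week 8 (day 58-60) sample.
3. Invite participants who stop early to give the week-8 sample all the same, and analyse them in their allocated group. This addresses the loss of drop-outs, which deleting the sentence alone would not.

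Section 7.4 already provides for replacing people excluded on their first blood result before the luminaire is installed, and that provision can stay.

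The cost is a change of wording and a slightly smaller primary analysis. One participant lost from one arm costs about 1 point of power one-sided (2 two-sided). Two lost from each arm cost about 5 points (7 two-sided). Week-8 samples from early stoppers would recover part of this. The change should be made before enrolment, so that the handling of replacements is not chosen with the data in view.

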### **7.6 Premature termination of the study**

Premature termination of the study is not expected to happen as no serious adverse effects are expected due to the lighting intervention or study protocol. Nevertheless, in case of a serious adverse effect has taken place, steps will be implemented to reduce these adverse effects. If necessary, the study will be terminated temporarily, until improvements have been implemented. If significant adverse effects persist, the study may be terminated prematurely. In that case, all participants and the reviewing accredited METC, will be informed.

## **8. SAFETY REPORTING**

### **8.1 Temporary halt for reasons of subject safety**

In accordance to section 10, subsection 4, of the WMO, the study will be suspended if there is sufficient ground that continuation of the study will jeopardise subject health or safety. The accredited METC will be notified without undue delay of a temporary halt including the reason for such an action. The study will be suspended pending a further positive decision by the accredited METC. The responsible investigator will take care that all subjects are kept informed.

